# Web-Based Group Conversational Intervention on Cognitive Function and Comprehensive Functional Status Among Japanese Older Adults: Protocol for a 6-Month Randomized Controlled Trial

**DOI:** 10.2196/56608

**Published:** 2024-07-11

**Keywords:** randomized controlled trial, web-based intervention, communication technology, cognitive health, neural blood markers, social isolation, well-being

## Abstract

**Background:**

Social communication is a key factor in maintaining cognitive function and contributes to well-being in later life.

**Objective:**

This study will examine the effects of “Photo-Integrated Conversation Moderated by Application version 2” (PICMOA-2), which is a web-based conversational intervention, on cognitive performance, frailty, and social and psychological indicators among community-dwelling older adults.

**Methods:**

This study is a randomized controlled trial with an open-label, 2-parallel group trial and 1:1 allocation design. Community dwellers aged 65 years and older were enrolled in the trial and divided into the intervention and control groups. The intervention group receives the PICMOA-2 program, a web-based group conversation, once every 2 weeks for 6 months. The primary outcome is verbal fluency, including phonemic and semantic fluency. The secondary outcomes are other neuropsychiatric batteries, including the Mini-Mental State Examination, Logical Memory (immediate and delay), verbal paired associates, and comprehensive functional status evaluated by questionnaires, including frailty, social status, and well-being. The effect of the intervention will be examined using a mixed linear model. As a secondary aim, we will test whether the intervention effects vary with the covariates at baseline to examine the effective target attributes.

**Results:**

Recruitment was completed in July 2023. A total of 66 participants were randomly allocated to intervention or control groups. As of January 1, 2024, the intervention is ongoing. Participants are expected to complete the intervention at the end of February 2024, and the postintervention evaluation will be conducted in March 2024.

**Conclusions:**

This protocol outlines the randomized controlled trial study design evaluating the effect of a 6-month intervention with PICMOA-2. This study will provide evidence on the effectiveness of social interventions on cognitive function and identify effective target images for remote social intervention.

**Trial Registration:**

UMIN Clinical Trials UMIN000050877; https://tinyurl.com/5eahsy66

**International Registered Report Identifier (IRRID):**

DERR1-10.2196/56608

## Introduction

Remote intervention, which allows interventions to be conducted remotely through communication technology with participants, may benefit health and convenience. Remote interventions enable people with low accessibility to interventions due to disability, illness, location, or pandemic to participate in interventions and provide equitable health service. In particular, there has been increased attention to internet-based social interventions that alleviate social isolation since the COVID-19 pandemic [1-3] because of increased social isolation reported [4].

Social isolation is a major public health concern and determinant of healthy longevity. According to Lancet Reports from the *Lancet* Commission on Dementia, social isolation has been identified as one of the single potentially modifiable risk factors for dementia [5]. A growing body of literature has reported a link between social interactions and the risk of dementia [6-9]. Recent longitudinal meta-analyses [10] have demonstrated the integrated risks of poor social interaction and greater loneliness with the occurrence of dementia. This meta-analysis suggests that the strength of this association is comparable to other well-established risk factors, such as low education, depression in later life, and poor physical activity.

Psychological, behavioral, and biological pathways may link social interactions to health. Social interaction may play a significant role in maintaining mental health [11,12] and could be an important contributing factor to dementia [13] by providing a sense of connection with others and buffering perceived stress. Social interactions may also have behavioral effects. Interacting with others may promote appropriate health behaviors [14,15] by providing access to health information and social support. Biological mechanisms may also be mediated by physiological processes involved in cardiovascular, immune, and neuroendocrine functions [16-18].

In addition, communication, the basis of social interaction, is an intellectual activity. Communication requires multiple cognitive processes. Furthermore, the multifaceted brain processes nonverbal information, such as the other person’s voice [19], facial expressions [20], and emotions [21], as well as a variety of verbal information during communication. Such cognitive stimulation through social and conversational activities can contribute to the maintenance of the cognitive abilities of an individual.

Based on the evidence, we hypothesized that social communication-based interventions would be effective in maintaining cognitive function. Consequently, a series of our previous randomized controlled trials (RCTs) examined the effect of structural face-to-face group conversation intervention and consistently observed some positive effects on verbal fluency [22,23]. Our explanatory investigation using multimodal magnetic resonance imaging identified the brain network, brain regions, and brain structure that could benefit from the intervention. Despite the significant limitation regarding the lack of preintervention data, we observed higher resting-state functional connectivity between the left inferior frontal gyrus as a seed region and the temporal pole and middle frontal gyrus, which may reflect the brain network involved in the intervention effects [24]. Our voxel-based morphometric analysis also identified the candidate brain regions involved in the intervention mechanism, including the lateral prefrontal cortex [25]. Further, analysis using diffusion tensor imaging metrics suggested that left frontal white matter structures were candidates for white matter microstructural changes effected by the intervention [26]. Building on these findings, we have inferred that our conversational intervention may stimulate language-related function in the prefrontal lobe, serving as a potential mechanism underlying the observed effects.

We recently focused on remote social intervention to address the challenges of the COVID-19 pandemic and clinical face-to-face interventions in which functional decline reduces accessibility to interventions. We developed a remote smartphone-based group conversation intervention program called “Photo-Integrated Conversation Moderated by Application” (PICMOA) and conducted a 12-week RCT to determine the effectiveness of the program [27]. The PICMOA trial showed a positive intervention effect on semantic fluency for those who were good at using smartphones before the intervention. On the other hand, potential issues for PICMOA intervention were also suggested, such as the difficulty of operating a small smartphone for older people, the psychological burden of using smartphones and apps for older adults, the possibility that the stimulation of visual social interaction is small due to the small smartphone screen, and the short intervention period.

To address these challenges of smartphone-based interventions for older adults in a past trial, we developed Photo-Integrated Conversation Moderated by Application version 2 (PICMOA-2), a remote conversational intervention for PC tablets. By adapting the intervention to a PC tablet, a larger screen is expected to improve operability for older people and increase cognitive stimulation through recognition of the speaker’s face.

The primary aim of this study is to evaluate the effect of a 6-month intervention with PICMOA-2 on cognitive function in community-dwelling older adults. In addition to investigating the intervention’s effects on cognitive function, this study also evaluates its impact on frailty and social and psychological indicators. We hypothesized that this intervention may have secondary effects, potentially contributing to the physical, mental, and social well-being of participants. These possible secondary effects could arise from the maintenance of cognitive function through our intervention or via other pathways such as stress buffering, behavioral changes, and physiological processes owing to the enhanced social interaction by the intervention. Furthermore, this study will address whether target attributes modify the intervention effects as a secondary objective, as it remains unclear whether web-based conversational intervention is effective for a broad population or only for a specific population.

## Methods

### Study Design

The PICMOA-2 trial is an open-label, 6-month RCT with 2 parallel groups, including 1 intervention group and 1 passive control group. The overall timeline of the procedure is shown as a SPIRIT flow in Table 1. The main and secondary outcomes will be assessed at baseline and after a 6-month intervention period.

**Table 1 table1:** Overall timeline of the procedure of the PICMOA-2 trial.

Time point				Enrollment		Allocation		Post allocation			Evaluation
				–t_1_		0		t_1_	t_2_		t_3_
**Enrollment**											
	Eligibility screening		✓		—^a^		—		—	—	
	Informed consent		✓		—		—		—	—	
	Allocation		—		✓		—		—	—	
**Interventions**											
	Practice using equipment and test session		—		—		✓		—	—	
	Interventions		—		—		—		✓	—	
**Assessments**											
	**List of baseline variables**										
		Demographic and socioeconomic information	✓		—		—		—	—	
		Lubben Social Network Scale-6	✓		—		—		—	—	
		Familiarity with using devices	✓		—		—		—	—	
	**List of outcome variables**										
		Mini-Mental State Examination	✓		—		—		—	✓	
		Verbal fluency tests	✓		—		—		—	✓	
		Logical Memory I and II	✓		—		—		—	✓	
		Verbal paired associates I and II	✓		—		—		—	✓	
		Kihon checklist	✓		—		—		—	✓	
		UCLA^b^ Loneliness Scale 10-item version	✓		—		—		—	✓	
		The 5-item World Health Organization Well-Being Index	✓		—		—		—	✓	
		Health Utility Index Mark 3	✓		—		—		—	✓	
		S-A creativity test	✓		—		—		—	✓	
	**List of other variables**										
		Blood-based biomarkers	—		—		✓		—	✓	
		Face scale	—		—		—		✓	—	

^a^Not applicable.

^b^UCLA: University of California, Los Angeles**.**

### Participants

We recruited community-dwelling older adults aged 65 years and older without cognitive decline living in Kishiwada city, Osaka Prefecture, Japan, near a metropolitan area with a population of 188,129 as of December 2023 [28]. This study’s design is illustrated in Figure 1. This procedure included eligibility screening, informed consent, outcome assessments, randomization, and 6 months of web-based conversational intervention. The inclusion criteria are as follows: a Mini-Mental State Examination (MMSE) score ≥ 24, available to provide written consent, and able to undergo the required tests and interventions on specified dates. We screened medical conditions and medication use and excluded patients with dementia; those with a history of disease or previous medications that could affect the central nervous system, such as neurological impairment, serious complicating disorders, and a history of serious head injury; and those certified as having a long-term care condition (“care needs levels” or “support need levels”) by the national public long-term care insurance system in Japan.

Participants were recruited by sending recruitment letters and flyers to community-dwelling older adults from the municipal government and posting announcements for enrollment in a new community paper. We mailed 3000 recruitment letters to randomly selected older adults without certificates of long-term care in 4 living areas of Kishiwada city. Some flyers were also distributed to the public and in collaboration with organizations. Once potential participants expressed interest in participating in the trial, they were screened for eligibility. Participants in both groups will receive cash compensation.

**Figure 1 figure1:**
[figure not shown]
Participant flow of the PICMOA-2 trial. MMSE: Mini-Mental State Examination; PICMOA-2: Photo-Integrated Conversation Moderated by Application version 2.

### Intervention

The intervention program is PICMOA-2, a web-based conversational intervention that uses a PC tablet at the participant’s home. Participants are instructed to take photos in their daily lives as much as possible according to the specific 12 themes during the 6-month intervention period and join conversational intervention based on PICMOA-2 once every 2 weeks for 6 months. Figure 2 describes the intervention structure of PICMOA-2. Participants are required to upload to the web system using a smartphone app that we originally developed before the intervention session, join the group conversational intervention session, and have a presentation and discussion about the photos that participants took during the session.

In the conversational session, each participant in a designated group of 4 gives a 1-minute speech about the 2 photos they took in their daily lives. Other participants then ask questions related to the photos, and the presenter answers the questions in the context of a natural conversation for 2 minutes for each photo. Research staff administer intervention using the PICMOA-2 system and support participants’ PC operations through remote access.

In the case of dropouts, substitutes are included in the group conversation to maintain the intensity of the intervention since different numbers of group members can lead to quantitative differences in the amount and duration of speaking, potentially impacting the effect sizes.

Smartphones for taking photos and PC tablets (Surface Go; Microsoft Corp) for conversational sessions with an internet connection were prepared for all participants.

**Figure 2 figure2:**
[figure not shown]
The intervention architecture. PICMOA-2: Photo-Integrated Conversation Moderated by Application version 2.

### Outcomes

#### Overview

Table 2 shows the overall outcome measurements.

**Table 2 table2:** The construction of outcome measurements.

Construction	Outcomes
Cognitive function	MMSE^a^, verbal fluency tests, Logical Memory I and II, and verbal paired associates I and II
Frailty	Kihon checklist
Loneliness	UCLA-LS 10^b^
Well-being	WHO-5^c^
Health-related quality of life	HUI3^d^
Divergent thinking	S-A creativity test

^a^MMSE: Mini-Mental State Examination.

^b^UCLA-LS 10: The University of California, Los Angeles Loneliness Scale-10 item version.

^c^WHO-5: 5-item World Health Organization Well-Being Index.

^d^HUI3: Health Utilities Index Mark 3.

#### Cognitive Functions

The main outcome measure is cognitive function. Specifically, we hypothesized that the PICMOA-2 may stimulate linguistic and executive functions through fundamental conversation activities based on the results of previous RCTs [22,23,27] and mechanistic hypothesis based on the explanatory investigation using multimodal magnetic resonance imaging [24-26]. Thus, we will specifically focus on verbal fluency as the primary outcome, which may reflect linguistic and executive functions. Well-trained clinical psychologists administered standardized neuropsychiatric tests to evaluate the effects of the intervention on cognitive function.

MMSE [29] is used to evaluate global cognitive function and screen for cognitive decline. The MMSE consists of 11 question sets and the total score is calculated. Verbal fluency tests, including 3 tasks each for semantic and phonemic fluency, are administered to assess linguistic and memory retrieval abilities, which may reflect executive control. A semantic fluency test is required to produce the names of animals, sports, and jobs, while the phonemic fluency test is required to generate the words that begin with the letter “a,” “ka,” and “si” in Japanese within 1 minute each. To evaluate episodic memory, Logical Memory I and II and the Verbal paired associates from the Wechsler Memory Scale-Revised [30] are introduced. Logical Memory is a story recall subtest. Logical Memory I assesses immediate recall and is required to immediately reproduce each of the 2 stories read out by the examiner, whereas Logical Memory II is required to reproduce stories approximately 30 (±5) minutes later to assess delayed recall. Verbally paired associates are paired-associate learning subtests. Participants are required to learn 4 pairs of related and unrelated words and test their memory of word pairs. Verbal Paired Association I assesses immediate recall, while Verbal Paired Association II assesses delayed recall approximately 30 (±5) minutes later.

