### Randomization and Blinding

Stratified block randomization, a block design (2, 4, and 6 block sizes) with a 1:1 allocation, was performed using the University Hospital Medical Information Network Internet Data and Information System for Clinical and Epidemiological Research Cloud version [39]. The participants were allocated to either the intervention or the control group. Sex (male or female) and MMSE scores (28 or higher and 27 or lower) at baseline were used for stratification. [name] is responsible for the randomization. As this study uses an open-label design, we aim to prevent potential assessment bias by blinding the assessors.

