### Statistical Analysis

This study evaluates the effects of the PICMOA-2 intervention on outcome measurements. Linear mixed models with random intercepts for outcome measurements will be used to estimate the intervention effects. Our model will include the group assignment factor, time factor, and group × time interaction term and evaluate the intervention effect from the interaction term. As a secondary aim, we will test whether the intervention effects varied with the covariates at baseline to examine the effective target attributes.

All analyses will be conducted using the R software (The R Foundation). Statistical significance will be set at *P*<.05.

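### The MMSE effect is read from a change-score comparison that uses the baseline score inefficiently, in a sample selected near the top of the scale

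*Protocol article*

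**What the plan says.** The Participants section recruits "older adults aged 65 years and older without cognitive decline" and requires "a Mini-Mental State Examination (MMSE) score ≥ 24". The Abstract ranks the outcomes: "The primary outcome is verbal fluency, including phonemic and semantic fluency", and "The secondary outcomes are other neuropsychiatric batteries, including the Mini-Mental State Examination". Table 1 places the MMSE at enrollment and at the final evaluation, with nothing in between.

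The Cognitive Functions section gives the test both of its roles: "MMSE [29] is used to evaluate global cognitive function and screen for cognitive decline". On scoring it says only: "The MMSE consists of 11 question sets and the total score is calculated". The Randomization and Blinding section adds a third use: "Sex (male or female) and MMSE scores (28 or higher and 27 or lower) at baseline were used for stratification".

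The Statistical Analysis section states one model: "Linear mixed models with random intercepts for outcome measurements will be used to estimate the intervention effects". Its terms are group, time and their interaction, and the interaction is the intervention effect. The MMSE is not treated separately. The article gives no baseline mean, SD or share at the maximum for the MMSE, and it does not print the maximum.

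**The concern.** Two features act on the same estimate.

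First, a random-intercept model with a free group difference at baseline, fitted to two visits, subtracts each participant's baseline score in full. When the before-after correlation is well below 1, this carries baseline noise into the effect estimate. Adjusting the 6-month score for baseline removes only the predictable part. The trial already collects the baseline MMSE and stratifies on it, so the information is there to use.

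Second, the entry rule admits only scores from 24 upward. With a maximum of 30, a participant in the upper randomisation stratum (28 or more) can gain at most 30 − 28 = 2 points, and one at 30 can only stay or fall. Part of a true improvement therefore cannot appear in the group × time estimate.

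At stake is the precision and reading of one secondary outcome, the only test that the article describes as measuring global cognition.

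**Working it through.** **Inputs from the article.** Entry at 24 or more; strata 28 or higher and 27 or lower; two visits; 66 randomised 1:1, so 66 / 2 = 33 per arm; two-sided 5%. **Assumed, because the article does not give them.** Scale maximum 30; underlying mean 27 to 29; SD 1.5 to 2; before-after correlation (reliability) 0.5 to 0.7; no dropout.

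**1. The plan's own figure.** The article gives no figure for the MMSE. Its one sizing figure, 65, comes back with an assumed correlation of 0.5: 54 evaluable participants give power 0.950 for f = 0.25, and 54 × 1.2 = 64.8, rounded up to 65. It does not bear further on this point.

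**2. What the model estimates.** With two complete visits, group × time equals (mean change, intervention) − (mean change, control), and its test is the t test on change scores.

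**3. Efficiency without a ceiling.** Let σ be the SD and ρ the before-after correlation.
- Residual variance, change score: 2σ²(1 − ρ).
- Residual variance, baseline-adjusted: σ²(1 − ρ²).
- Ratio, adjusted to change: (1 + ρ) / 2. At ρ = 0.6 this is 0.80.

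For a 0.5 SD effect with 33 per arm, the noncentrality is 0.5 / √(variance / σ²) × √(33/2):
- change score: 0.5 / √0.80 × 4.062 = 2.27, power 0.61;
- baseline-adjusted: 0.5 / √0.64 × 4.062 = 2.54, power 0.71.

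That is about 10 points of power before any ceiling. The same formulas give 0.52 against 0.64 at ρ = 0.5, and 0.73 against 0.80 at ρ = 0.7.

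**4. Efficiency with the entry rule and ceiling.** Scores were simulated, rounded, capped at 30 and admitted only at an observed baseline of 24 or more. Reliability was 0.6, SD 2, the gain 0.5 SD, with 33 per arm.

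| Simulation | Assumed mean | Change score | Linear, baseline-adjusted | Proportional odds |
|---|---|---|---|---|
| A | 28 | 0.49 | 0.61 | 0.62 |
| A | 28.5 | 0.48 | 0.57 | 0.61 |
| A | 29 | 0.43 | 0.58 | 0.63 |
| B | 28 | 0.47 | 0.62 | 0.64 |
| B | 29 | 0.38 | 0.51 | 0.49 |

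The gain from linear adjustment is 12, 9, 15, 15 and 13 points. Simulation A used about 420 to 510 runs per setting, so each power has a Monte Carlo standard error near √(0.5 × 0.5 / 450) = 0.024. Proportional odds minus linear adjustment is +1, +4, +5, +2 and −2 points, which is not a reliable difference.

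**5. Size of the ceiling loss.** Same set-up with correlation 0.5 and a true 1-point difference. The power columns refer to the change-score test of a gain.

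| Mean, SD | At 30 at baseline | Observed gain (true 1.0) | Power, no cap | Power, capped | Share kept if the effect is 1 point less decline |
|---|---|---|---|---|---|
| 27, 1.5 | 5% | 0.95 | 0.76 | 0.72 | 99% |
| 27, 2.0 | 11% | 0.89 | 0.53 | 0.48 | 96% |
| 28, 1.5 | 16% | 0.84 | 0.77 | 0.66 | 95% |
| 28, 2.0 | 23% | 0.77 | 0.52 | 0.44 | 89% |
| 29, 1.5 | 37% | 0.63 | 0.75 | 0.54 | 84% |
| 29, 2.0 | 40% | 0.59 | 0.51 | 0.34 | 77% |

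**6. Type I error.** With no effect, the change-score test rejected in 5.1% to 5.6% of runs. In simulation A all three analyses rejected in 3% to 6%.

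**The case against.** Several stronger readings are tempting, and the article does not support them.

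- **That the ceiling removes any gain.** Participants at 24 to 27 have 3 to 6 points of room. The loss is partial, and at a mean near 27 it is small. The stratification cut at 28 suggests many high scorers but does not establish the distribution.
- **That the Gaussian model is at fault.** Its type I error holds, and under randomisation it estimates the difference in observed mean change. That difference is too small only against an uncapped score, which the article never names as its target. The limit lies in the instrument used in this population.
- **That a null MMSE result would be taken as no effect.** No section says so. The MMSE is one of several secondary measures, and the Limitations section already calls for larger-scale validation. Power for a 1-point difference is only about 0.5 to 0.77 even without a cap, so a null result would be inconclusive anyway.
- **That an ordinal model must replace the linear one.** Its margin over linear adjustment is within simulation noise. It also gives up an effect in points and adds a proportional-odds assumption over sparse categories with 66 participants.

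Two further objections stand in part. The introduction and discussion also frame the aim as maintaining function or slowing decline, and in that case the ceiling matters much less. Detailed handling of a secondary outcome may sit in an analysis plan that is not shown, so silence about the ceiling is not itself a fault. What remains is the model that the article does state, which makes poor use of a baseline score already in hand.

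**Conclusion.** The point holds as a minor improvement to the analysis of one secondary outcome. As stated, the MMSE effect is a change-score comparison. Conditioning on the baseline score instead adds roughly 12 to 15 percentage points of power for a half-SD gain at an assumed reliability of 0.6 with 33 per arm. One simulated setting gave 9, and the formula without a ceiling gives 10. The advantage shrinks as reliability rises.

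Separately, selection near the maximum hides about 5% to 40% of a true gain under assumed means of 27 to 29 and SDs of 1.5 to 2. If the effect is less decline, 1% to 23% is hidden. Baseline adjustment improves precision but does not restore what the ceiling hides, so the share at the maximum is needed to read the estimate. All these sizes rest on assumed distributions and a maximum of 30. Type I error is intact. The ceiling does not reach verbal fluency, for which the article states no upper limit.

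**What to change.** In the Statistical Analysis section, add that the MMSE effect is estimated from the 6-month score adjusted for the baseline MMSE score. Either linear ANCOVA or the equivalent mixed model will do, with a common baseline mean for both groups and an unstructured covariance across the two visits. The mixed model also keeps participants who have no 6-month score. Report the number and share at the scale maximum at each visit by group, beside the estimate. A proportional-odds model of the 6-month score given baseline may be listed as a sensitivity analysis. Eligibility and stratification stay as they are.

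The cost is one or two sentences and a different model call in R. No new data are needed, and the effect stays in MMSE points.
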